## Concomitant Therapy

### Allowed Therapy

Participants can take bupropion or varenicline.

### Required Therapy

Participants will be required to participate in the on-site, standard cessation treatment that includes behavioral counseling and pharmacotherapy that includes nicotine replacement therapy provided by their medical team at the Tom Waddell Urban Health Clinic, Richard H. Fine People’s Clinic, and the Positive Health Program Clinic. It is possible that participants may recive counseling from different members of the medical team. We will be tracking this through follow-up questionnaires, as well as within the EHR through receipt of counseling (i.e., medical assistant, behavioral assistant and/or PCP counseling) and medications for cessation. HIPPA trained study staff will be trained to extract data on weekly receipt of counseling from the EHR. Two study staff will provide the incentive payments for demonstration of abstinence.

### Prohibited Therapy

Not applicable.

## Participant Discontinuation/Withdrawal from the Study

Participants are free to withdraw from participation in the study at any time upon request.

An investigator may discontinue a participant from the study for the following reasons:

- Unacceptable adverse event(s)
- Significant study intervention non-compliance, unless varying compliance is an aspect of the study objectives
- Lost-to-follow up; unable to contact participant (see Section 5.7 - Lost to Follow-Up)
- Any event or medical condition or situation occurs such that continued collection of follow-up study data would not be in the best interest of the participant or might require an additional treatment that would confound the interpretation of the study
- The participant meets an exclusion criterion (either newly developed or not previously recognized) that precludes further study participation

## Lost to Follow-up

A participant will be considered lost to follow-up if he or she fails to return for a scheduled visits and study staff are unable to contact the participant after at least 3 attempts. Before a participant is deemed lost to follow-up, the investigator or designee will make every effort to regain contact with the participant (where possible, 3 telephone calls and, if necessary, a letter to the participant’s last known mailing address or local equivalent methods). These contact attempts will be documented in the participant’s study file. Should the participant continue to be unreachable, he or she will be considered to have withdrawn from the study with a primary reason of lost to follow-up.

Participants will be asked to provide and update contact information at each visit. If a participant does not present for their scheduled visit, study staff will call the participants, or contact the participant’s contacts, or visit the places the participant reported that they spend time. Between the 6 month and 12 month assessment, participants will be asked and incentivized to check-in monthly by phone or in-person. We will hire two people who will assist with recruitment and retention efforts – patients seeking care at the TWUHC, RFPC, or PHP who have experienced homelessness and not participating in the trial – who will assist in contacting participants who are lost to follow-up.^52,53^ We have used these tracking procedures successfully in prior studies that have had a similar frequency of visits and length of follow-up.^61-63,65-69^ Based on prior work, we expect retention rates of 85% at 2 weeks, 85% at 3 months, and over 75% at 6-months and 1-year follow-up.^61-63,65-69^

# Study Procedures and Assessments

Participants will be asked to choose a quit date within 7 days of providing consent,^26,30,32,33,100^ and will meet study staff at the TWUHC, RFPC, or PHP on the day of the quit attempt (Table 3). Participants will meet daily for the first 7 days (week 1), twice weekly for the next 3 weeks (1 month), once weekly for the next 9 weeks (3 months), and monthly until the one-year follow-up (1 year). Assessment visit schedule is identical for both groups. At each of the scheduled assessment visits, participants will provide a CO sample and complete a short questionnaire on cigarette consumption, quit attempts since the last visit, the length of the last quit attempt, and use of medications and services. Questionnaires will be built on REDCap, and administered by study staff using an iPad. At enrollment, 2 weeks, 1 month, 3 months, 6 months, and 1-year follow-up, participants will be asked to complete structured questionnaires.

## Schedule of Activities

| **Assessments/Procedures** | **Screening** |  |  | **Study Intervention Period** |  | **End of Study Intervention** | **Follow-up** |
| --- | --- | --- | --- | --- | --- | --- | --- |
| **Study Visit / Day**  **(Window, # Days)** | **Visit -1/enrollment** | **Visits 2-8 / Week 1**  **Daily assessment** | **Visit 9-14 / Weeks 2- 4**  **Bi-weekly assessment** | **Visits 15-22/Weeks 5-13**  **Weekly assessment** | **Visits 23-25/Weeks 16-24**  **Monthly assessment** | **Visit 27 / Week 52**  **1 year follow-up** |  |
| Informed Consent^[[1]](#footnote-2)^ | **X** |  |  |  |  |  |  |
| Inclusion/Exclusion Criteria | **X** |  |  |  |  |  |  |
| Medical Record Review | **X** | **X** | **X** | **X** | **X** | **X** | **X** |
| Concomitant Medications | **X** | **X** | **X** | **X** | **X** | **X** |  |
| Adverse Events | **X** | **X** | **X** | **X** | **X** | **X** | **X** |
| Randomization/Assignment to Intervention | **X** |  |  |  |  |  |  |
| Administration of Study Intervention |  | **X** | **X** | **X** | **X** |  |  |
| Protocol-Specific Assessments/Procedures^2^ | **X** | **X** | **X** | **X** | **X** | **X^3^** | **X** |

## Study Procedures and Assessments

### Screening Period / Visit -1 (Day -0 to Day 1)

After an individual provides informed consent, the following activities will be performed during the Screening Period:

- Inclusion/exclusion criteria review
- Medical record review – smoking status and housing status
- Review of concomitant medications
- Adverse Events assessment
- Protocol-specific assessments/procedures
- Randomization/Assignment to Intervention

### Study Intervention Period

#### Visits 2-8 (Week 1)

- Review of concomitant medications
- Adverse Events assessment
- Administration of Study Intervention: Contingent incentives for smoking cessation
- Protocol-specific assessments/procedures: Daily expired carbon monoxide sample and a brief questionnaire

#### Visits 9-14 (Weeks 2-4)

- Review of concomitant medications
- Adverse Events assessment
- Administration of Study Intervention: Contingent incentives for smoking cessation
- Protocol-specific assessments/procedures: Expired carbon monoxide sample and a brief questionnaire bi-weekly; Questionnaires at 2 weeks and 1 months follow-up

#### Visits 15-23 (Week 5-13)

- Review of concomitant medications
- Adverse Events assessment
- Administration of Study Intervention: Contingent incentives for smoking cessation
- Protocol-specific assessments/procedures: Expired carbon monoxide sample and a brief questionnaire weekly; Questionnaires at 3 months follow-up;

#### Visits 24-26 (Weeks 16-24)

- Review of concomitant medications
- Adverse Events assessment
- Administration of Study Intervention: Contingent incentives for smoking cessation
- Protocol-specific assessments/procedures: Expired carbon monoxide sample and a brief questionnaire monthly between 3 and 6 months; Questionnaires at 6 months follow-up; At 6 months follow-up, if participants self-report abstinence, and have an expired carbon monoxide level < 5ppm, then we will collect a urine sample for anabasine/anatabine analysis.

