# Study Objectives and Endpoints

## Primary Objective

| **Primary Objective** | **Endpoint(s)** | **Time Frame** |
| --- | --- | --- |
| 1. Assess feasibility and acceptability of measuring biochemically-verified point prevalence abstinence at 6 months follow-up. | Evaluate the proportion of participants who achieve biochemically-verified 7-day point prevalence abstinence defined as participants (1) reporting not smoking a single cigarette in the past seven days, not even a puff; (2) having CO levels ≤5 ppm, and (3) anatabine/anabasine assays <2 ng/ml. | Baseline to 6 months follow-up |
| 1. Assess feasibility and acceptability of adhering to the protocol | Total number of carbon monoxide negative samples | Baseline to 6 months follow-up |
| 1. Assess feasibility and acceptability of gathering information on the number of visits attended | Total number of visits attended | 6 months |
| 1. Assess feasibility and acceptability of the retention protocol | Proportion of the sample retained as a result of retention procedures | 2 weeks, 1 month, 3 months, 6 months, and 12 months follow-up |

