# Study Intervention

## Administration and/or Delivery of Study Intervention

**Usual smoking cessation care at TWUHC, RFPC, and PHP**. Patient participants will be required agree to attend usual smoking cessation care that is available to all clinic patients who receive clinical services at the clinic. Usual cessation care includes weekly one-on-one counseling by on-site behavioral counselors and pharmacist-dispensed NRT (i.e., transdermal patch, the gum or lozenge, the primary cessation medications in this clinical trial) covered by health insurance for at least 12 weeks.

| **Table 1: Escalating Contingency Management Schedule for Intervention Group^** | | | | |
| --- | --- | --- | --- | --- |
|  | Visit frequency | # of Visits | Intervention group potential earnings | |
|  |  |  | Total for time period | Average per visit |
| Week 1 | Daily | 7 ($13.00-16.00) | $101.50 | $14.50 |
| Weeks 2 – 4 | Bi-weekly | 6 ($16.50-19.00) | $106.50 | $17.75 |
| Weeks 5 – 13 | Weekly | 9 ($19.50-23.50) | $193.50 | $21.50 |
| Weeks 14– 24 | Monthly | 3 ($24.00-25.00) | $73.50 | $24.50 |
| Total (6 months) |  | **25** | **$ 475** |  |
| ^ Incentive payment begins @ $13.00 and increases by $0.50 for each consecutively negative CO sample (<5 ppm) to a maximum of $24.50 for the last sample. | | | | |

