**Intervention.** In addition to receiving usual cessation care, CM intervention participants with CO-verified abstinence will obtain a CM incentive payment, via gift cards redeemable in national retail chains, according to a pre-defined schedule. Gift card amounts and assessment frequencies are based on prior studies among individuals experiencing homelessness or with substance use disorders,^26,30,32,33,38^ and are expected to be effective in promoting smoking cessation. We think this CM schedule is close to what will be adopted; however, our results from Aim 1 will inform the protocol. Gift card amounts will begin at US $13 and increase by $0.50 for each negative CO specimen throughout the first 6 months of the program to a maximum of $24.50 per specimen for a total of 25 specimens collected through week 24 (Table 3). An escalating schedule that increases per visit incentive payment over time is especially important in this study to maintain motivation as visit frequency decreases over time. The total amount that participants can earn under the contingent incentive program through week 24 is $620, an amount comparable to what has been used in prior studies.^30-33^ Test results indicative of smoking (i.e. CO >5ppm) or missed visits will lead to resetting the gift card amount back to the initial low value, but two consecutive negative tests will restore the value back to the highest level previously achieved. ^26,30,32,33,100^

**Control condition.** Control group participants will receive a fixed amount of $5 for attending each abstinence assessment visit and participate in usual cessation care, as described above.^32^ This approach has been used in a prior study of CM for smoking cessation among homeless adults.^32^

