**Abstinence assessment schedule*.*** All other aspects of the study protocol will be identical across the two experimental groups. Participants will be asked to choose a quit date within 7 days of providing consent,^26,30,32,33,100^ and will meet study staff at TWUHC or ZSFG on the day of the quit attempt (Table 1). Participants will meet daily for the first 7 days (week 1), twice weekly for the next 3 weeks (1 month), once weekly for the next 9 weeks (3 months), and monthly until the one-year follow-up (1 year). Assessment visit schedule is identical for both groups. At each of the scheduled assessment visits, participants will provide a CO sample and complete a short questionnaire on cigarette consumption, quit attempts since the last visit, the length of the last quit attempt, and use of medications and services. Questionnaires will be built on REDCap, and administered by study staff using an iPad.

***Abstinence assessment.*** As in prior studies, ^26,30,32,33,100^to determine eligibility for CM, we will assess point-prevalence abstinence with CO monitoring, using a cut-off of CO≤ 5 parts per million (ppm).^98^ For primary outcome assessment, we will confirm abstinence among participants who self-report abstinence and meet criteria for abstinence based on CO with urinary anatabine and anabasine (i.e. metabolites of tobacco) using a cut-off of <2 ng/ml ^101^ (analyzed by the UCSF Cancer Center Tobacco Biomarkers Core ^102^). Urinary anatabine and anabasine are tobacco alkaloids that are useful as confirmatory biomarkers to verify abstinence among patients who are using NRT for smoking cessation, and for whom urinary cotinine would not be appropriate.^101^

**Data collection reimbursements*.*** We will reimburse all participants with $20 for completing the baseline questionnaire, $15 each for questionnaires at 2, weeks, 1 month, and 3 months, and $25 each for questionnaires at 6 months and 1-year follow-up. Between 6 and 12 months, all participants will receive $5 for checking in at each monthly visit and providing a CO specimen. The total amount that all participants could earn for 1 year of participation exclusive of CM is $145 and as much as $620 inclusive of CM ($145+$475).

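### The protocol gives two conflicting CO triggers for the urine sample that the 6-month primary abstinence endpoint requires: ≤5 ppm in Section 5.1, <5 ppm in the visit procedure

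*Protocol*

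**What the plan says.** **Endpoint.** Protocol Section 2.1 defines the 6-month primary abstinence endpoint by three components that must all hold. The first is self-report of no smoking in the past seven days; the others are "2) having CO levels ≤5 ppm, and (3) anatabine/anabasine assays <2 ng/ml". Section 5.1, under the clinical outcomes for the future full-scale trial, repeats the same definition.

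**Urine trigger, Section 5.1 (abstinence assessment).** The CO limit is set "using a cut-off of CO≤ 5 parts per million (ppm"). For the primary outcome the section then states: "we will confirm abstinence among participants who self-report abstinence and meet criteria for abstinence based on CO with urinary anatabine and anabasine". Read together, these call for urine from self-reported abstainers with CO of 5 ppm or less.

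**Urine trigger, Section 6.2.2 (Visits 24-26, Weeks 16-24).** The visit procedure states: "if participants self-report abstinence, and have an expired carbon monoxide level < 5ppm, then we will collect a urine sample for anabasine/anatabine analysis". This excludes a reading of exactly 5 ppm.

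**Incentive rules, Section 5.1.** The Table 1 footnote says that the payment "increases by $0.50 for each consecutively negative CO sample (<5 ppm) to a maximum of $24.50 for the last sample". The text on the intervention says: "Test results indicative of smoking (i.e. CO >5ppm) or missed visits will lead to resetting the gift card amount". The footnote puts 5 ppm outside negative; the text does not treat 5 ppm as smoking.

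**The concern.** The trigger for collecting a specimen should admit everyone who can still meet the endpoint that the specimen serves. Here the visit procedure is narrower than the endpoint by one value. A person at that value passes two components and is then denied the test for the third.

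Three features make this worth raising despite its small size. The rule can only remove people from the count of verified abstainers. A urine sample not taken at 6 months cannot be obtained at analysis. And the first primary objective is the feasibility of measuring this very endpoint, which the protocol carries forward as the primary outcome of the full-scale trial, so the mismatch could carry forward with it.

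The same split affects a second primary endpoint in Section 2.1, the total number of CO-negative samples. The Table 1 footnote is the only place that attaches a number to a negative sample, and its limit differs from the limit that the Section 5.1 text implies.

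**Working it through.** The plan gives no figure of its own to reproduce on this point: Section 9.1.1 offers no power analysis. The check compares the limits and then applies simple arithmetic to the stated arm size.

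**Step 1. The limits side by side.**

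| Place in the Protocol | Purpose | Limit | Is 5 ppm included as abstinent or negative? |
| --- | --- | --- | --- |
| Section 2.1; repeated in 5.1 | Primary endpoint, component (2) | ≤5 ppm | Yes |
| Section 5.1, abstinence assessment | CM eligibility and, through the CO criterion, urine confirmation | ≤5 ppm | Yes |
| Section 6.2.2, Visits 24-26 | Urine collection at 6 months | <5 ppm | No |
| Section 5.1, Table 1 footnote | Negative sample for escalation | <5 ppm | No |
| Section 5.1, intervention text | Result indicative of smoking (reset) | >5 ppm | Yes, by implication |

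**Step 2. The gap.** {CO ≤5} minus {CO <5} = {CO = 5 ppm}. At 5 ppm, component (2) is met (5 ≤ 5 is true), but the Section 6.2.2 trigger is not (5 < 5 is false). No assay is run, so component (3) cannot be shown.

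**Step 3. Size per person.** Section 4.6 gives 45 per arm and 90 in total. Assume that all randomized participants form the denominator and that unverified people count as not abstinent. Each affected person who would have passed the assay then lowers the arm's proportion by 1/45 = 0.022, or 2.2 percentage points, and the overall proportion by 1/90 = 0.011, or 1.1 points.

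**Step 4. Range.** The documents give no distribution of CO readings, so the expected number is unknown. Two illustrations, both resting on assumed inputs:

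- 0 to 3 such people in one arm: 0/45 to 3/45 = 0 to 6.7 points.
- 20% of 45 = 9 people reporting abstinence with CO ≤5 ppm, of whom 5% to 15% read exactly 5: 9 × 0.05 = 0.45 to 9 × 0.15 = 1.35 people. Divided by 45, this is 1.0 to 3.0 points.

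Both treat every 5 ppm reader as someone who would have passed the assay, so each is an upper bound under its own inputs. Both also assume that the monitor can return a reading of exactly 5 ppm.

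**Step 5. After alignment.** With ≤5 ppm in both places the gap is empty. Everyone who passes the first two components has urine collected. No sample size or power figure changes.

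**Step 6. Reach.** The 3-month, 12-month and prolonged-abstinence endpoints in Section 2.2 need only self-report and CO ≤5 ppm. They require no urine, so this gap does not touch them.

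**The case against.** The strongest case on the other side has four parts.

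**The loss is not inevitable.** A reader of Section 6.2.2 alone might infer that someone at 5 ppm can never be verified. The documents do not support that. Section 5.1 calls for urine from self-reported abstainers who meet the CO criterion, and its cut-off includes 5 ppm. The loss arises only if staff follow the visit procedure rather than Section 5.1. This objection stands: the fault is two conflicting triggers. It does not remove the point, because a visit list is what staff are likely to work from.

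**Payment at 5 ppm is not undefined.** The footnote and the reset rule, taken alone, suggest that 5 ppm falls between negative and smoking. But the ≤5 ppm cut-off in Section 5.1 is stated there as the test of eligibility for CM, and the reset rule at >5 ppm agrees with it. Only the Table 1 footnote is out of line. Nor does the mismatch bear on the fidelity outcome: Table 2 measures whether payments that are due are delivered within 2 days, which is timeliness.

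**The size is not established.** The 1.0 to 3.0 points rest on an abstinence rate and a share of 5 ppm readings that the documents do not give. Without urine, the true status of those people is unknown. This stands; only the effect per person is firm.

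**The consequences are limited.** Section 9.3 proposes no inferential statistics and judges feasibility against the Table 2 thresholds, none of which is an abstinence rate. The trigger is the same in both arms. This stands and sets the severity.

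**Conclusion.** The contradiction is real, and it is minor. Sections 2.1 and 5.1 agree on ≤5 ppm; the visit procedure in Section 6.2.2 departs from them at exactly 5 ppm. If the visit procedure is followed, a self-reported abstainer at that reading meets components (1) and (2) and cannot be assessed on (3).

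The number of verified abstainers can then only be too low, by 2.2 points of an arm's proportion for each affected person who would have passed the assay. That figure assumes a denominator of 45 and that unverified people count as not abstinent. How many people would be affected cannot be determined from the documents.

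The inconsistency in the Table 1 footnote is separate. It matters here because the number of CO-negative samples is itself a primary endpoint and would depend on which limit is used to count.

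**What to change.** - **Urine trigger.** In Section 6.2.2, Visits 24-26, align the CO condition for urine collection with component (2) of the primary endpoint (≤5 ppm, as in Sections 2.1 and 5.1). Check that the REDCap branching at the 6-month visit uses the same limit. This concerns outcome measurement only.
- **Negative sample.** Reconcile the Table 1 footnote with the CO limits in the Section 5.1 text, and state in Section 2.1 which limit defines a CO-negative sample for the endpoint that counts them. The sponsor should settle which limit governs the incentive schedule.

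The cost is a few wording changes, a check of the form logic and perhaps one or two extra urine assays. The correction has to be in place before 6-month visits take place, since samples missed by then cannot be recovered.

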### End of Study Intervention / Visit 27 (Week 52)

- Review of concomitant medications
- Adverse Events assessment
- Protocol-specific assessments/procedures: Expired carbon monoxide sample and an exit questionnaire at 12 months follow-up

### Follow-up

Participants will be followed daily for the first week, bi-weekly between 2 and 4 weeks, weekly for 4 weeks to 13 weeks, monthly from 16 weeks to 1 year after discontinuing the study intervention. The following procedures will be performed at each follow-up time point:

- Medical record review
- Adverse Events assessment

# Reporting and Documentation of Results

## Measures and Instruments

We will develop surveys in RedCap using our previously validated instruments in this population. Questionnaire measures will include:

| **Table 3: Questionnaire measures** |
| --- |
| **Sociodemographics**: Age, sex (male, female, transgender), race/ethnicity, education, monthly income, health insurance, health status, marital status |
| **Residential history**: Lifetime and past 6-months history of homelessness ^55^ |
| **Alternative tobacco and nicotine produce use:** Ever, past 30-day use of cigarettes and frequency of use of non-cigarette tobacco and nicotine products.^103^ |
| **Nicotine dependence:** Fagerstrom Test for Nicotine Dependence,^104^ Smoking urges,^105^ Confidence to quit.^103^ |
| **Cessation history**: Intention to quit, quit attempt (ever and in the past year), length of last quit attempt, use of cessation aids (medications, telephone quit line, health care provider advice ) ^97^ |
| **Substance use history**: Alcohol,^106^ and Substance Involvement Screening Test version 3.0 (WHO-ASSIST) during lifetime and in the past 6 months.^107^ |
| **Mental health disorders:**  Mini International Neuropsychiatric Interview v.6.0 ^108-111^ |
| **Chronic health conditions:** Self-reported chronic health conditions^112^ |

*Sociodemographic, residential history, and health status.* We will obtain information on age, sex (sex assigned at birth, current gender), race/ethnicity, education, monthly income (i.e. income from all sources), marital status, health insurance, and health status.^113^ For residential history, we will ask where participants had stayed the previous night (unsheltered, emergency shelter, transitional shelter, single room occupancy hotel, supportive housing). We will ask questions to assess whether they currently meet HEARTH criteria for homelessness,^96^ when their current episode of homelessness began, and when they were last stably housed.

*Nicotine dependence and tobacco cessation history.* We will assess Fagerstrom’s test for nicotine dependence,^104^  smoking urges,^105^ confidence to quit.^103^ We will assess cessation history including intention to quit, quit attempt (ever and in the past year), length of the last quit attempt, and use of cessation aids during the last quit attempt (e.g., medications, telephone quit line).

*Alternative tobacco and nicotine product use.* We will obtain information on ever use and use in the past 30 days of non-cigarette tobacco and nicotine products including electronic cigarettes, cigars, little cigars, smokeless tobacco, hookah/waterpipe, cannabis, and blunts.

*Chronic Diseases.* We will ask participants whether they have liver, renal, or cardiovascular disease, hypertension, diabetes, cancer, chronic obstructive pulmonary disease, or HIV.^114^

*Mental health.* We will conduct the Mini International Neuropsychiatric Interview v.6.0 (MINI 6.0),^108,115-117^ a brief structured interview that has been validated for assessing DSM-IV and ICD-10 psychiatric diagnoses (lifetime and current diagnosis for major depression, bipolar I and II, posttraumatic stress disorder, psychotic disorders, and generalized anxiety disorder).

*Alcohol and Substance Use and Use Disorders.* We will administer the Alcohol, Smoking and Substance Involvement Screening Test version 3.0 (WHO-ASSIST).^107,118-120^ In order to assess volume of alcohol consumed, we will administer the consumption questions from the Alcohol Use Disorders Identification Test (AUDIT-C).^106,121^

